### 2.9. Sources of Bias

Major sources of bias in this protocol relate to selection bias and self-reported data, both of which are inherent sources of bias in observational studies [37,38]. We acknowledge that individuals volunteering to participate in the study (as in most clinical studies) may be from a pool of participants who might be better educated, of higher socioeconomic status, or health-motivated [37]. This protocol aims to employ analytical strategies to summarise and adjust for various health and demographic characteristics and has been reported in the statistical section. Like many other cross-sectional/observational studies, this protocol relies on a significant amount of self-reported data from participants. This introduces an inherent source of bias in self-collected data, and it cannot be avoided [38]. Researchers will thoroughly check all self-collected data and revise hardcopy and electronically submitted questionnaires with participants to ensure correct interpretation of questionnaires and that correct data have been entered by participants.

### 2.10. Ethics and Dissemination

#### 2.10.1. Ethics

This study has been approved by the University of Newcastle’s Human Research Ethics Committee (HREC 2020-0195). Eligibility will be assessed by lead investigators by phone or in person using the eligibility checklist. Eligible volunteers will be provided with the information statement, and written informed consent will be obtained. Findings will be reported to PBDS participants; funding bodies and institutes; and federal, state, and local governments to inform policy (should opportunity arise); findings will be presented at local, national, and international conferences and disseminated by peer-reviewed publications.

#### 2.10.2. Participant Safety

All risks to the participants in the study will be mitigated by ensuring recruitment and data collection are managed by appropriately trained and experienced research investigators with all the required certifications and qualifications. Recruitment will be undertaken by Accredited Practising Dietitians with extensive experience in clinical research recruitment and dietary interventions to ensure accurate and thorough conduct of dietary screening and eligibility. Data will be stored in a secure setting, with password-protected devices and cloud storage systems. All participants are required to complete a DXA Safety Screening Questionnaire on the day of their DXA scan, and all scans will be performed by trained technicians according to standard operating procedures by the external service provider, Newcastle Bone Density Centre. A dosimetry report by a medical physicist has also been obtained for this protocol, deeming radiation exposure associated with this study to be safe with negligible risk. A trained phlebotomist will conduct all venepuncture blood sample collections under standard operating procedures.

#### 2.10.3. Unexpected Findings during Examinations

At the end of the study appointment, participants will be provided with their personal study results, i.e., body composition output, blood pressure, and FFQ survey results outlining food and nutrient intake in accordance with national recommendations. Routine blood test results analysed by the service provider will be provided to participants as soon as they are received by the researchers via the participants nominated preferred method of contact, e.g., email or post. All participants will be encouraged to visit their General Practitioner should they have any questions or concerns regarding any of their personal results. The researchers will not provide any health advice or recommendations based on clinical findings from this study.

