### 2.6. Clinical Assessments and Laboratory Investigations

#### 2.6.1. Blood Sampling and Analyses

Fasted blood samples will be collected via venepuncture into Vacuette^®^ blood tubes by an experienced phlebotomist. Samples will be centrifuged (Heraeus Biofuge Stratos, Germany, Heidelberg, sourced from Australia) for 15 min at 3000× *g* at 4 °C. Plasma, red blood cells, and buffy coat fractions will be aliquoted and stored at −80 °C until further analysis. Biochemical parameters, such as lipids (total cholesterol, LDL-cholesterol, HDL-cholesterol, triglycerides, and total-cholesterol-to-HDL-cholesterol ratio); glycaemic indices (glucose, insulin, and HbA1c); vitamin D (25-hydroxy vitamin D); full blood count; liver function, and high-sensitive C-reactive protein will be measured on a VP auto analyser using standardized reagents by the commercial pathology service provider NSW Health Pathology–North. Pro-inflammatory mediators, such as interleukin, tumour necrosis factor α, and intercellular adhesion molecule-1, will be quantified by enzyme-linked immunosorbent assay as per the manufacturer’s instructions (Abcam, Cambridge, UK) at the Nutraceuticals Research Program, University of Newcastle, (Callaghan, NSW, Australia). Polygenic risk scores will be measured to predict the likelihood of specific outcomes by including DNA variants in a statistical model.

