The PBDS commenced recruitment on 10 November 2021, and despite having some delay due to the COVID-19 pandemic, we have been able to recruit individuals from the community, with several participants already enrolled into each of the dietary pattern categories. The study remains in the recruitment and data collection phase until at least mid-2023 before data cleaning, coding, and analyses will commence. The study is expected to be completed by mid-2024. As with many observational studies, some of the data collected in this study are self-reported; however, several of the data collection tools employed in this study have been validated in Australian populations. To further mitigate any risk associated with self-reported data, all data are cross-checked by study researchers and clarified (when required) with participants to their ensure accuracy and the correct interpretation of the questionnaires or instructions. As with all cross-sectional population-based studies, caution must be exercised when inferring causation from the results. As detailed in the protocol, appropriate statistical analyses will be conducted to summarise and adjust for the confounding factors and covariates, and a senior biostatistician will be involved in the project.

To conclude, given several strengths and the significance of this study’s findings, albeit with some limitations, analysis of the data arising from this study will likely influence nutrition policy and dietetic practice around the influence of ‘plant-forward’ eating patterns for heart health.

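### Section 2.10.3 makes GP review depend on the participant's own concern, and its unqualified ban on recommendations does not except a staff prompt about a markedly abnormal result

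*Protocol article*

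**What the plan says.** Section 2.10.3 (Unexpected Findings during Examinations) makes four statements, in this order.

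1. At the end of the appointment, "participants will be provided with their personal study results, i.e., body composition output, blood pressure, and FFQ survey results".
2. Blood results follow later: "Routine blood test results analysed by the service provider will be provided to participants as soon as they are received by the researchers", and they go "via the participants nominated preferred method of contact, e.g., email or post".
3. On what the participant should do with them: "All participants will be encouraged to visit their General Practitioner should they have any questions or concerns regarding any of their personal results".
4. On what the researchers may say: "The researchers will not provide any health advice or recommendations based on clinical findings from this study".

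Section 2.6.1 shows which laboratory values are involved. Besides lipids, "glycaemic indices (glucose, insulin, and HbA1c); vitamin D (25-hydroxy vitamin D); full blood count; liver function, and high-sensitive C-reactive protein will be measured". Section 2.10.2 (Participant Safety) opens with "All risks to the participants in the study will be mitigated by ensuring recruitment and data collection are managed by appropriately trained" and goes on to dietary screening, data security, the DXA scan and venepuncture. It has no step for results once they are returned.

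**The concern.** The section is headed for unexpected findings, yet its one rule on what researchers may say makes no exception for the serious case. Statement 3 depends on the participant having a question or a worry. Statement 4 rules out recommendations as well as advice. Telling a person to see a GP because a particular value is markedly abnormal is, in plain words, a recommendation based on a clinical finding.

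At stake is the participant who receives such a value and does not see that it matters. This can happen here. Participants are aged 35 to 75 with no history of CVD, and Section 2.1 deliberately includes people with chronic conditions. Section 2.6.5 defines diabetes status by current treatment and a reported diagnosis, so undiagnosed diabetes would show only as a returned glucose or HbA1c value, and the person would have no earlier reason to be concerned.

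**Working it through.** The plan has no figure to reproduce. The check is a reading of the four statements of Section 2.10.3 against two kinds of participant.

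| Participant with a markedly abnormal result | Statement 3 (GP prompt) | Statement 4 (ban) | Outcome under the text |
|---|---|---|---|
| Recognises it and asks | Applies | Limits the researcher to pointing to the GP | Directed to the GP |
| Does not recognise it | Its condition is not met | Makes no exception for a staff prompt | No stated prompt to act |

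The first row shows that a GP route exists and covers all participants and all of their results. The second row is the gap.

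**Does another section fill the second row?** Section 2.10.2 does not. No other section of the article gives a referral that staff initiate, or an exception to statement 4.

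**Where is the gap most concrete?** It is in the blood results. They are sent after the visit, by a route such as email or post, and the section mentions no conversation alongside them. That silence does not show that none takes place. Blood pressure is returned face to face at the end of the appointment, so the remote-delivery point does not apply to it. Only the wording of the ban does.

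**How many are affected?** This cannot be calculated. The documents give neither the rate of markedly abnormal results nor the share of recipients who would fail to act.

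**Which trigger would be proportionate?** This calculation bears only on the remedy and is no evidence of harm. Section 2.6.1 names 10 single routine measures (5 lipid, 3 glycaemic, vitamin D, hsCRP) plus the blood count and liver panels. Assume 10 to 20 independent tests, each with a 95% reference range. The chance that a healthy person has at least one value out of range is then:

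- 10 tests: 1 − 0.95^10 = 0.401, and 0.401 × 240 ≈ 96 people
- 20 tests: 1 − 0.95^20 = 0.642, and 0.642 × 240 ≈ 154 people

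Correlation between tests, as among the lipids, would lower these figures. Even so, a trigger on any out-of-range value would flag too many healthy people to be useful. The exception should be confined to markedly abnormal results.

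**The case against.** The strongest reply is that the last sentence should not be read apart from the one before it. Together they say that the study returns the results, the GP interprets them, and the researchers do not advise. On that reading, sending someone to a GP is the stated route and not the thing forbidden. This is a natural reading and it largely stands. A reader might infer from the ban alone that staff have no way at all to direct a participant to a GP. The documents do not support that, because the preceding sentence offers the GP to everyone. The reply does not remove the condition in that sentence, which still leaves the start to the participant.

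A second reply is that alert thresholds and escalation steps belong in the full protocol or the ethics application, which are not shown. That is right, and their absence from a journal article is no finding. A reader might also infer that the study has no escalation procedure, or that this sentence conflicts with one. Neither can be shown, since no such procedure is available to compare. The point rests only on a rule that the article does state, without an exception.

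A third reply is that laboratory reports may already flag abnormal values, so that participants would notice them. The documents do not say whether they do. The remedy therefore must not depend on flags alone.

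Finally, limiting what a research team advises is a legitimate boundary. That stands, and the proposed wording keeps it.

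**Conclusion.** The point holds in a narrow form. Section 2.10.3 states a GP route, but one that only the participant can trigger, and the ban that follows does not except a staff-initiated recommendation of GP review for a markedly abnormal result. It is a minor participant-safety matter of wording.

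Its size cannot be quantified from the documents. It has no bearing on the sample size, the data or the analysis: each person is measured once and feedback follows measurement. The conclusion assumes that the sentence is applied as written. If staff already follow the softer reading, the change only makes their practice explicit.

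**What to change.** Replace the last sentence of Section 2.10.3 with:

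*Researchers will not diagnose or give treatment or lifestyle advice. This does not prevent them from telling a participant that a result is markedly abnormal (by cuts agreed with the ethics committee, or by a provider flag where reports carry one) and recommending GP review, whether or not the participant raises a concern.*

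For blood results, put that recommendation in the email or letter that carries them.

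The cost is a short ethics amendment, one line in the results message when it is needed, and a few extra GP visits.

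Timing limits the reach. Recruitment began in November 2021, and the article says "The study remains in the recruitment and data collection phase until at least mid-2023". An amendment would help only those of the planned 240 not yet measured. If the ethics committee agrees, one pass through the results already on file would extend it to the others.

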#### 2.10.4. Dissemination

The findings from analysis of the PBDS will be disseminated in various platforms, such as manuscripts in peer-reviewed journals and scientific conference abstracts, presentations, posters, and a higher degree research thesis. These will also be reported to local, state, and federal governments to inform policy and new and revised national dietary guidelines. Findings from this cross-sectional study may inform the development of specific dietary guidelines for PBDs as well as inform current dietary guidelines related to cardiovascular health. Reports made to funding bodies and institutes that supported the PBDS will also be made from these study findings. Members of the research team will have publishing and authorship rights in accordance with National Health and Medical Research Council Australian Code for the Responsible Conduct of Research and as described in research agreements.

## 3. Discussion

The PBDS is an Australian-first cross-sectional study exploring the cardiovascular health and dietary profile of PBDs. The novelty of this cross-sectional study pertains to the methodological design of purposeful recruitment of habitual consumers of various PBDs and meat-eating diets. Previous studies examining the link between PBDs and cardiometabolic health have been secondary analyses in cohorts not primarily designed to investigate the association between PBDs and cardiometabolic diseases. Moreover, myriad different terms and characteristics have been used when defining various PBDs, leading to discrepancies and possibly to misclassification. The globe’s growing adoption of sustainable dietary patterns alongside major health authorities, such as the World Health Organization (WHO) and the Food and Agriculture Organization of the United Nations (FAO), emphasising plant-forward eating highlights the critical need for population-based evidence to guide the safe and effective implementation of these dietary patterns in Australia. This work will identify the dietary profile and nutrition implications of various PBDs currently adopted by Australians alongside their impact on cardiometabolic risk factors. This study will provide a database for future cross-sectional investigations exploring characteristics of PBD in Australia and linking PBD and health. Moreover, this work will serve as a body of evidence with which to develop a well-defined longitudinal study to examine the association between PBDs and the development of chronic diseases over time.

There is a need to establish population-specific, appropriate, and up-to-date cardiovascular risk prediction equations for Australians [17]. The absolute risk equation (based on the Framingham Risk Equations) currently used in Australia may overestimate risk in individuals under 30 years of age [19] and underestimate CVD risk in specific populations, such as Aboriginal and Torres Strait Islander peoples, South Asian, Māori, and Pacific Islanders, and Middle Eastern persons; adults with diabetes; adults aged over 74 years adults with depression; and adults who are socioeconomically disadvantaged [19]. To mitigate this, the current study will not include individuals aged under 30 years nor those over 70 years, and a large breadth of additional CVD risk factors and lifestyle characteristics/behaviours will be collected from the participants’ medical history: physical measures, including body composition, biochemical parameters, socio-economic and demographic characteristics, and dietary intake. Investigation of these significant risk factors that are not currently included in the risk equations will provide extra predictive value and inform the overall interpretation of the risk of developing CVD in association with dietary patterns explored in this study.

The novel outcomes of the PBDS include the following: (1) investigation of the 5-year and 10-year risk of developing CVD across the spectrum of PBDs and meat-eating dietary pattern; (2) analysis of biological samples to understand the biological mechanisms driving cardiometabolic health outcomes/risk across dietary patterns; (3) investigation and analysis of diet intake, quality, and nutritional adequacy across the spectrum of PBD and meat-eating dietary patterns; (4) development of rich data that characterise the health, socio-economic, behaviour, and medical history of individuals following PBD and meat-eating dietary patterns to improve the understanding of the interplay between PBDs and CVD risk; and (5) implementation of standardised definitions of a PBD in the Australian population in an epidemiological setting. To our knowledge, there is no other cross-sectional study within Australia or internationally where all these five points are explored in a single study with this design.

The PBDS commenced recruitment on 10 November 2021, and despite having some delay due to the COVID-19 pandemic, we have been able to recruit individuals from the community, with several participants already enrolled into each of the dietary pattern categories. The study remains in the recruitment and data collection phase until at least mid-2023 before data cleaning, coding, and analyses will commence. The study is expected to be completed by mid-2024. As with many observational studies, some of the data collected in this study are self-reported; however, several of the data collection tools employed in this study have been validated in Australian populations. To further mitigate any risk associated with self-reported data, all data are cross-checked by study researchers and clarified (when required) with participants to their ensure accuracy and the correct interpretation of the questionnaires or instructions. As with all cross-sectional population-based studies, caution must be exercised when inferring causation from the results. As detailed in the protocol, appropriate statistical analyses will be conducted to summarise and adjust for the confounding factors and covariates, and a senior biostatistician will be involved in the project.

To conclude, given several strengths and the significance of this study’s findings, albeit with some limitations, analysis of the data arising from this study will likely influence nutrition policy and dietetic practice around the influence of ‘plant-forward’ eating patterns for heart health.

## Figures and Tables

**Figure 1 nutrients-15-02850-f001:**
[figure not shown]
Flow diagram of the overall study design for the PBDS:DEXA, Dual X-ray absorptiometry scan; FFQ, food frequency questionnaire.

**Figure 2 nutrients-15-02850-f002:**
[figure not shown]
Directed acyclic graph showing independence among potential confounding and mediating variables on the association between PBDs and CVD risk. Confounding factors are age, sex, alcohol use, smoking status, and physical activity levels, and BMI is a mediator. BMI, body mass index; PBDs, plant-based diets; CVD, cardiovascular disease.

**Table 2 nutrients-15-02850-t002:** Classification of dietary pattern groups by the number of time(s) foods are consumed, on average, per week.

	Vegan	Lacto-Ovo Vegetarian	Semi-Vegetarian	Pesco-Vegetarian	Regular Meat-Eater
Times per week consumed:					
Red meats:	0	0	≤1	0	0 or ≥1
Beef, kangaroo, veal, lamb, pork, etc.					
White meats:	0	0	≤1	0	0 or ≥1
Chicken, turkey, duck, etc.					
Processed/cured meats:	0	0	≤1	0	0 or ≥1
Bacon, corned beef, luncheon meats, such as ham, prosciutto, salami, etc., sausages, frankfurters					
*Seafood:* Fish (including tinned), crustaceans, oysters, squid, mussels, etc.	0	0	0 or ≤1	≥1	0 or ≥1
**Total of above categories**	0	0	≤2	≥1	≥7
Usual eating habits					
Animal-based dairy products (milk, cheese, ice-cream, butter, cream, margarine blends, etc.)	Nil	Y	N/A	N/A	N/A
Eggs	Nil	Y	N/A	N/A	N/A

Defining characteristics of dietary patterns are adapted from those previously implemented in Australian cohorts by Ferguson et al. [12] and Mihrshahi et al. [10]. ‘N/A’ denotes characteristics that were not relevant and, thus, not used for categorizing into respective diet groups.

**Table 3 nutrients-15-02850-t003:** Questionnaires, histories, measures, and biochemical samples completed by participants unaided and with assistance of a study investigator.

Item	Measures and Tools	Collected by Researcher or Participant ^1^
Medical history, medication/supplement use, and family medical history	Medical and Demographic Questionnaire	Participant
Demographics, ethnicity, socio-economic status, education history, employment history, smoking history, habitual alcohol intake, marital status, household food, and social history	Medical and Demographic Questionnaire	Participant
Physical activity	International Physical Activity Questionnaire (IPAQ-Long Form 2002) [13]	Participant
Dietary intake (qualitative), diet quality	Australian Eating Survey Food Frequency Questionnaire (AES FFQ) [14]	Participant
Food and nutrient intake (quantitative) and dietary pattern characteristics	Diet history via Accredited Practicing Dietitian	Researcher
Fasted biochemical parameters	Venepuncture blood sample	Researcher
Blood pressure and waistline	Seated systolic and diastolic blood pressures Waist circumference	Researcher
Height and body composition	Dual X-ray absorptiometry scan	Researcher

^1^ Collected by participant via self-administered questionnaire.

**Table 4 nutrients-15-02850-t004:** Qualitative risk categories used to describe calculated 5-year absolute CVD risk using the Australian Absolute CVD Risk Calculator and 10-year CVD risk using the Framingham Risk Equation.

Risk Category	5-Year CVD Risk Description ^1^	10-Year CVD Risk Description ^2^
**Low risk**	<10% probability of CVD within the next five years	<10% probability of CVD within the next ten years
**Moderate/Intermediate risk**	10–15% probability of CVD within the next five years	10–20% probability of CVD within the next ten years
**High risk**	>15% probability of CVD within the next five years	>20% probability of CVD within the next ten years

^1^ Guidelines for the assessment of absolute CVD risk [20]. ^2^ Categories of absolute CVD risk percentage over 10 years, classified according to previous studies [21,22].

